#### Sample size

The primary outcome in this study is shoulder ROM, which is the main effect indicator for sample size estimating in this randomized controlled trial. Referring to Cohen’s effect size value of 1.3799 in the study of Başkaya et al. [25], to achieve 95% power and 0.05 error range, 30 of the total sample size were calculated using the G-power 3.1 software. However, a larger sample size was planned to be used in this trial due to repeated measurement. We used the GLIMMPSE software for repeated measurement calculation with the shoulder flexion range of motion as the main effect indicator that refers to the results of Başkaya et al. [25]. We choose a test power of 0.95 and a type 1 error rate of 0.05, 58 of sample size was calculated, considering 20% dropout rate, the actual total sample size is 70.

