### Randomization and blinding

Random number sequences are generated in the randomization software by an independent researcher; the 200,000 was used as the seed number to generate 70 random numbers. For avoiding tampering or transillumination, information of trial was written on the two layers of carbonless copy paper, which was placed in sealed, opaque, sequentially numbered envelopes. An independent research assistant will conduct the group allocation. Participants are required to write their name and admission number on the first layer of paper after disclosing the envelopes, random number sequence and group allocation can be seen only on the second layer of paper, and once the two layers of paper are separated, it cannot be restored. After participants sign the informed consent, the rater completes the baseline assessment, then the research assistant who is blinded to the study will perform the group allocation. Eligible participants will be randomly divided into either the MT group or the control group in a ratio of 1:1. After disclosing the envelope, the participant who obtains a paper marked with the number “1” will be allocated to the MT group, while the participant who obtains a paper marked with “2” will be grouped to the control group. Because of the nature of the intervention, rehabilitation therapists and nurses are not blinded, but they are not informed of the trial purpose; the rater, research assistant, and statistician are blinded, and they are also asked not to seek the group allocation and intervention from participants.

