### Data analysis

Data analysis will be processed by an independent statistician and primary researcher using the SPSS24.0 software. All statistical tests will be double sides; the statistical significance is set at *p* value < .05. Means and standard deviation or median and inter-quartile ranges will be calculated for continuous variables normally distributed and non-normally distributed, respectively. Categorical variables will be described as frequencies (*f*) and percentages (%). Demographics and other baseline values will be analyzed using the independent two-tailed *t*-test, non-parametric Mann-Whitney *U*-test, and chi-square test.

This study will adopt the modified intention-to-treat (mITT) principle. The effects of the intervention on primary and secondary outcomes (excluded arm circumference and incidence of lymphedema) between the groups will be analyzed by generalized estimating equation (GEE) from treatment, time points, and the interaction between group and time. Observed values of those outcomes at four assessments time points will be put into GEE, selecting the auto-correlation matrix and the robust standard error estimation method. Taking outcome index as the response variable, the group, time, and interaction of group and time will be incorporated into the model, in addition, selecting radiotherapy, the dominant hand, and type of surgery as covariates. The model includes the main effect and interaction effect, paired comparison variables will be selected, and the least significant difference (LSD) method will be used to adjust the multiple comparison effect. Arm circumference and incidence of lymphedema will be analyzed at each measurement time point between groups using the independent two-tailed *t*-test and chi-square test. In case of missing data, if missing data is completely random, the sample will not be included in the final data analysis. If missing data is incomplete random missing or non-random missing, multiple interpolations will be used to complete missing values.

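### With 56 to 70 women, the GEE with robust standard errors, read plainly, tests at about 6% (single contrast) and 7-8% (group-by-time) instead of 5%

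*Protocol article*

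**What the plan says.** The Data analysis section of the Protocol article fixes the estimator in some detail. Outcomes other than arm circumference and lymphedema "will be analyzed by generalized estimating equation (GEE) from treatment, time points, and the interaction between group and time". Baseline is part of the response: "Observed values of those outcomes at four assessments time points will be put into GEE". With four time points and two groups, the interaction therefore has 3 degrees of freedom. The model is adjusted by "selecting radiotherapy, the dominant hand, and type of surgery as covariates", and fitted by "selecting the auto-correlation matrix and the robust standard error estimation method". The software is SPSS 24.0. On the level, "All statistical tests will be double sides; the statistical significance is set at" p < .05.

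The section names neither a small-sample correction to the robust variance nor a t or F reference distribution.

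The Sample size section arrives at 58 women and then, "considering 20% dropout rate, the actual total sample size is 70". Allocation is 1:1 (Randomization and blinding).

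**The concern.** The sandwich variance and its normal or chi-square Wald test are large-sample results. With 28 to 35 women per arm, two errors push in the same direction. The variance is estimated with divisor n rather than n-1, so standard errors are slightly small. The cut-offs (1.96 for one contrast, 7.815 on 3 df) also ignore that the variance is itself estimated.

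The group-by-time test is how this model asks whether mirror therapy changes recovery across visits. It estimates a 3 x 3 covariance matrix and suffers most. The issue applies to every outcome analysed by GEE, including shoulder range of motion, and matters for results near the threshold.

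**Working it through.** **Inputs from the Protocol article.** Alpha 0.05 two-sided; four time points; group, time and group-by-time in the model; 1:1 allocation; 58 calculated; 20% dropout; 70 planned. The planned total reproduces as 58 x 1.2 = 69.6, rounded to 70. A 20% loss from 70 leaves 70 x 0.8 = 56. So N runs from 56 (n = 28 per arm) to 70 (n = 35).

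**Assumed, because not stated.** Plain sandwich variance and the usual Wald reference. The closed form also takes complete, normal data and no covariates; it needs no value for the within-woman correlation.

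**One contrast.** The estimates are then the arm-by-visit means, and the robust variance is (n-1)/n times the unbiased one. The test rejects when |t| on N-2 df exceeds 1.960 x sqrt((n-1)/n).
- N = 56: 1.960 x sqrt(27/28) = 1.960 x 0.9820 = 1.925, so the level is 5.95%.
- N = 58: 5.92%.
- N = 70: 1.960 x sqrt(34/35) = 1.960 x 0.9856 = 1.932, so the level is 5.76%.

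**3-df group-by-time test.** It rejects when Hotelling's T² exceeds 7.815 x (n-1)/n, with F = T² x (N-4) / (3 x (N-2)) on 3 and N-4 df.
- N = 56: T² = 7.536; F = 7.536 x 52/162 = 2.419, so the level is 7.66%.
- N = 58: 7.56%.
- N = 70: T² = 7.591; F = 7.591 x 66/204 = 2.456, so the level is 7.07%.

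**Interval width against the exact t interval.** N = 56: 0.9820 x 1.960/2.005 = 0.960. N = 70: 0.9856 x 1.960/1.995 = 0.968. Intervals are 3-4% too narrow from both causes combined.

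**Separating the causes (same closed form).**

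| Source | One contrast, N = 56 / 70 | 3 df, N = 56 / 70 |
|---|---|---|
| Small standard error alone (ratio 0.982 / 0.986) | 5.43% / 5.34% | 5.66% / 5.53% |
| Normal or chi-square reference alone | 5.52% / 5.41% | 6.89% / 6.48% |
| Both | 5.95% / 5.76% | 7.66% / 7.07% |

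For one contrast the two causes are about equal. For the 3-df test the reference distribution is the larger one.

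**Simulation under the null.** 8,000 trials per setting, AR(1) working correlation and robust standard errors. True correlation was AR(1) with 0.3 or 0.6, or exchangeable with 0.6. Runs were with and without four covariate dummies of assumed prevalence, and with normal or skewed errors. Monte Carlo error is about 0.25-0.3 points.

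| Test | N = 56 | N = 70 |
|---|---|---|
| Group-by-time contrast at week 8 | 5.6-6.2% | 5.5-6.0% |
| Group difference at week 8 | 5.8-7.1% | 5.4-6.8% |
| 3-df group-by-time | 7.4-8.2% | 6.5-7.5% |

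**Remedies in the same simulations.** The single contrast here is the group-by-time contrast at week 8.
- Mancl-DeRouen standard error with t/F on N-2 df: 4.3-5.1% (one contrast) and 4.7-5.5% (3 df).
- The same standard error with normal/chi-square cut-offs kept: 4.7-5.3% and 5.6-6.7%. The reference must change too.

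**Mixed model, by closed form.** With unstructured covariance and about N-2 denominator df, the 3-df test uses F cut-offs of 2.776 (N = 56) and 2.740 (N = 70). Multiplied by (N-4)/(N-2), these are 2.673 and 2.659 on 3 and N-4 df, which gives 5.7% and 5.5%.

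**The case against.** The strongest reply is that the article never says the robust variance is uncorrected, gives no divisor and names no reference distribution. Such details often sit in a fuller analysis plan, and GEE with robust standard errors is a recognised method for repeated measures. This stands as a limit: a fuller plan could remove the problem, so the finding holds for the method as written. It does not dispose of the point, because the article does choose estimator, standard error, software and level, and on their plain reading these do not give the stated level.

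Second, the size is modest. One contrast is off by about one percentage point, in a trial whose Objectives call it exploratory. The unadjusted handling of multiple tests is a larger matter: four independent tests, one per range-of-motion direction, would alone give 1 - 0.95^4 = 18.5%. This also stands, and it keeps the point minor.

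Third, the simulated figures rest on assumed correlations and covariate prevalences, and no calculation models the planned multiple imputation, under which the analysed number need not fall to 56. That is fair. But the closed form needs no correlation, and the inflation is still present at N = 70.

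**Conclusion.** The point holds and is minor. On the plain reading of the Data analysis section, with 56 to 70 women, the level is about 6% for a single contrast (5.4-7.1% across simulated settings) and about 7-8% for the 3-df group-by-time test (6.5-8.2%), against the stated 5%. It rests on no small-sample correction being applied and on the usual Wald reference being used; the closed-form values also assume complete normal data without covariates.

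Three stronger readings go too far:
- A reader might infer that small standard errors explain the whole excess. Without covariates they are only 1.4-1.8% too small, and alone give at most 5.4% (one contrast) and 5.7% (3 df).
- A reader might infer that the trial's error control fails outright. The excess is small and would matter only for borderline results, not for an effect near the 1.3799 cited in the Sample size section.
- A reader might blame the auto-correlation matrix or the unequal visit spacing. Neither enters the closed form, which already shows the inflation.

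**What to change.** Keep the mean model (group, time, group-by-time and the three covariates) and add one sentence on inference. There are two options.

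1. GEE with a small-sample-corrected sandwich, for example Mancl-DeRouen, **and** t or F reference distributions on about N-2 degrees of freedom. Both parts are needed. This gave 4.3-5.1% and 4.7-5.5% in simulation. Nothing in the article shows that SPSS 24.0 offers the correction, so other software may be required.
2. A linear mixed model with unstructured covariance over the four time points and Satterthwaite degrees of freedom. By the closed form this brings the 3-df test to about 5.5-5.7%: much closer to 5%, but not exact.

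If a fuller analysis plan already specifies a correction and reference distribution, it is enough to state them in the Data analysis section. Either option makes intervals slightly wider and p-values slightly larger. Participants, visits and data collection are unaffected.

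### The plan says LSD will adjust for multiple comparisons, but LSD leaves each pairwise p-value unadjusted: about 8–14% family-wise error over three post-operative visits on one movement

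*Protocol article*

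**What the plan says.** The Data analysis section of the protocol article fits a generalized estimating equation to each outcome, apart from arm circumference and lymphedema. The model has group, time and their interaction, with all four assessments as responses. It then continues: "The model includes the main effect and interaction effect, paired comparison variables will be selected". The correction it names for these pairwise tests comes in the same sentence: "the least significant difference (LSD) method will be used to adjust the multiple comparison effect". For testing in general it states "All statistical tests will be double sides" and "the statistical significance is set at *p* value < .05".

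The Primary outcome section lists four movements (forward flexion, internal rotation, external rotation, abduction) and ranks none above the others. The Sample size section uses flexion for the repeated-measures calculation: "We choose a test power of 0.95 and a type 1 error rate of 0.05, 58 of sample size was calculated". No visit is named as primary. Nothing makes the pairwise tests conditional on a significant interaction. The Objectives section calls the trial exploratory.

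**The concern.** The sentence gives a named procedure a property it does not have. LSD compares each pairwise p-value with the unadjusted 0.05, so three visit comparisons are three chances at a false positive. This is not a detail left to a later document: the article fixes the method and describes it wrongly.

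What is at stake is how the result is read. If one visit shows p = 0.03 for a movement and the other two do not, a reader told that the comparisons were adjusted will take that visit as established. With no adjustment made, an isolated finding of this kind is considerably more likely to be chance than the reader would suppose.

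**Working it through.** **Inputs.** Two-sided level 0.05 per test (Data analysis). Four assessments, of which three are post-operative, at 2, 4 and 8 weeks (Outcomes measures). Hence k = 3 between-group contrasts per movement. The correlation of the test statistics between visits is not given, so it is assumed at 0.3 to 0.9.

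**1. The plan's own figure.** The Sample size section takes an "effect size value of 1.3799 in the study of" the mirror-therapy trial in adhesive capsulitis and reports: "to achieve 95% power and 0.05 error range, 30 of the total sample size were calculated using the G-power 3.1 software". A two-sample t-test with the noncentral t distribution, two-sided 0.05 and 1:1 allocation, gives:
- 15 per arm: noncentrality 1.3799 × √(15/2) = 3.779, critical value 2.048, power 0.954;
- 14 per arm: power 0.940, which is too low.

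The total of 30 therefore reproduces, as a calculation for one two-sided contrast at 0.05. The later figure of 58 cannot be recomputed, because the article does not give the means, SDs and correlations behind it.

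**2. LSD over three visits, independent.** Family-wise error = 1 − (1 − 0.05)³ = 1 − 0.857 = 0.143.

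**3. LSD over three visits, correlated.** This was simulated as three null z-statistics with any |z| > 1.96 counted as an error. AR(1) used 400,000 draws and equal correlation used 2,000,000.

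| Assumed correlation | AR(1) | Equal correlation |
|---|---|---|
| 0.3 | 13.7% | 13.6% |
| 0.5 | 12.9% | 12.5% |
| 0.7 | 11.5% | 10.9% |
| 0.9 | 8.8% | 8.4% |

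The range is about 8–14%.

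**4. With a real adjustment.** Bonferroni tests each contrast at 0.05/3 = 0.0167. Under the complete null, Holm makes at least one false rejection exactly when Bonferroni does. The family-wise error is then 4.8% to 3.1% (AR(1), correlation 0.3 to 0.9), and 4.8% to 3.0% with equal correlation.

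**5. If a gate were added.** Suppose pairwise tests were made only after a significant three-degree-of-freedom group-by-time test. With AR(1) correlation 0.3 to 0.9:
- with no effect at any visit, the family-wise error is 3.2% to 0.9%;
- with a large true effect at 2 weeks only, false positives at 4 or 8 weeks occur in 9.5% to 7.1% of trials.

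A gate controls error when nothing is happening, but not when one visit differs.

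**The case against.** **The trial calls itself exploratory, and the group-by-time test is sound.** Both points stand. The interaction is one test per outcome, and LSD does not inflate it. In an exploratory trial, unadjusted visit contrasts are defensible if they are labelled as such. Neither point rescues the sentence, which says the contrasts are adjusted. The trial also names a primary outcome and tests at 0.05.

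**Fisher's protected LSD may have been intended.** No gate is stated. One would help under the complete null but would leave 7.1–9.5% in the partial-effect case of step 5.

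**A stronger reading is tempting: that the plan promises 5% over the whole primary outcome and delivers 46%.** Over four movements and three visits, 1 − 0.95¹² = 46.0% if all 12 tests were independent. The documents do not support laying this on the LSD sentence, for two reasons:
- The 0.05 is stated as a significance threshold and as a sample-size input. It is nowhere promised across 12 contrasts.
- Much of the 46% comes from having four unranked movements. That is a separate matter, which adjusting over visits does not cure: with each movement held at 5%, 1 − 0.95⁴ = 18.5% would remain if movements were independent.

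A reader might also count all 28 pairs among the 2 × 4 = 8 group-by-visit means. Most of these mix groups and visits or compare times within a group. The article does not say that all would be used as evidence of efficacy.

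**Conclusion.** The concern holds as an error in the stated method: LSD does not do what the Data analysis section says it does, and nothing else in the article supplies the missing control. For one movement and three post-operative between-group contrasts, the family-wise error is 14.3% under independence and about 8–14% for assumed correlations of 0.9 to 0.3, against at most 5% with a real adjustment. These figures assume that the three contrasts are read as a family, that no gate is applied, and that the test statistics are approximately normal. The group-by-time test is unaffected. The fault is plain but narrow, and it is cheap to correct.

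**What to change.** Remove the statement that LSD adjusts. That is the minimum. Then choose one of the following:

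- **Adjust.** Apply Holm, sequential Bonferroni or sequential Sidak to the between-group contrasts at 2, 4 and 8 weeks. Name those three contrasts as the family, and check that the software adjusts that set and not all pairs of the eight means. This controls error within one movement. To cover the whole primary outcome, also name one primary movement or treat all 12 contrasts as one family.
- **Pre-specify.** Make one movement at one visit the single primary contrast, tested at 0.05. Flexion is the natural candidate, since the sample size already rests on it. Label every other pairwise p-value unadjusted and descriptive.

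The cost is one changed sentence and a small change to the analysis, with no new data or participants. Under Holm some pairwise p-values rise, for the primary outcome as well as for secondary ones. The smallest of three is multiplied by 3, so 0.03 becomes 0.09. The second option leaves p-values unchanged but gives up confirmatory claims on the other contrasts.

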### Potential advert events and exercise adherence

The nurse needs to regularly record the volume of fluid drainage, as well as observe the wound and measure arm circumference. Adverse events include but are not limited to wound drainage volume increases over 50 ml 1 week later after the operation, delayed wound healing, seroma, skin flap necrosis, and persistent shoulder pain. Any adverse event occurring after the entry into this study of participants will be truthfully recorded. The participant who reports adverse events will have the right to withdraw and get free treatment, as well as evaluation. If participants wish to continue the intervention, we still provided exercise to them. Adherence to exercise is deemed to be an attendance of 85% of planned exercise sessions, which is a total of 261 sets. Adherence will be calculated according to the records of the exercise log.

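### The missing-data rule drops women whose data are judged missing completely at random, and gives non-random missingness an imputation with no stated adjustment for it

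*Protocol article*

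**What the plan says.** Everything at issue is in the Data analysis section of the protocol article.

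- Analysis set: "This study will adopt the modified intention-to-treat (mITT) principle". The article does not define the modification.
- Model: "Observed values of those outcomes at four assessments time points will be put into GEE", with group, time and their interaction, and robust standard errors.
- Missing data, first rule: "if missing data is completely random, the sample will not be included in the final data analysis".
- Missing data, second rule: "If missing data is incomplete random missing or non-random missing, multiple interpolations will be used to complete missing values". I take this to mean multiple imputation.

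The section names no method for deciding which mechanism applies, and states no adjustment or sensitivity analysis for non-random missingness. The Sample size section plans for 20% dropout in a total of 70.

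**The concern.** The two rules fit their conditions badly.

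Under missing completely at random (MCAR), a GEE on the available visits is already valid. A woman seen at baseline, 2 weeks and 4 weeks but not at 8 weeks has three usable assessments, and dropping her gains nothing. It also removes a randomised woman, which sits badly with an analysis described as modified intention-to-treat.

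The second rule gives missing at random (MAR) and missing not at random (MNAR) the same remedy. Standard multiple imputation assumes MAR, so it suits the first case and leaves bias in the second.

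Between the two lies a switch: who is analysed, and how, depends on a judgement about the mechanism made after the data are in. MAR and MNAR cannot be told apart from observed data, and in a trial this small a test may well miss a departure from MCAR. At stake are the precision of the primary comparison and, if MCAR is wrongly accepted, its freedom from bias.

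**Working it through.** **The plan's own figures.** For an effect size of 1.3799, two-sided 0.05 and power 0.95, a noncentral-t calculation gives 15 per arm, 30 in total (power 0.954), as stated. The 58 from the repeated-measures software cannot be re-derived because its SDs and correlations are not given. The total follows as 58 × 1.2 = 69.6, rounded to 70. Planned dropout is 0.20 × 70 = 14, leaving 56. Whether 58 was inflated correctly is a separate matter.

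**Step 1: deletion when MCAR is true.** Assume a probability q of missing each of the three post-operative visits, independently, and read the sample as the participant. Complete cases number 70 × (1 − q)³:

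| q | Complete cases of 70 |
|---|---|
| 5% | 70 × 0.857 ≈ 60 |
| 7% | 70 × 0.804 ≈ 56 |
| 10% | 70 × 0.729 ≈ 51 |
| 20% | 70 × 0.512 ≈ 36 |

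At q = 7%, the post-operative records observed are 70 × 3 × 0.93 ≈ 195. Complete cases keep 70 × 3 × 0.804 ≈ 169, so about 26 observed records are discarded.

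For the simple week-8 difference, available cases number n(1 − q) and complete cases n(1 − q)³, so the variance ratio is about 1/(1 − q)². That is 1/0.93² = 1.16 at 7% and 1/0.80² = 1.56 at 20%. Simulation (35 per arm, AR(1) correlation 0.6, 5,000 trials) gave:

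- q = 7%: SD 0.267 against 0.248, variance ratio 1.16.
- q = 20%: SD 0.337 against 0.267, variance ratio 1.59.
- Bias below 0.002 SD throughout, for both analyses.

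If women instead leave for good after the 2-week visit, the gain from keeping them comes only through correlation with their earlier visits. A simulation of that pattern gave a standard error of 0.267 with deletion and 0.258 with all data: (0.267/0.258)² = 1.07. Hence the range of 7% to 59%.

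**Step 2: deletion when MCAR is wrongly accepted.** Assume 35 per arm, visit correlation 0.6, about 20% dropout in the mirror-therapy arm driven by poor range of motion at 2 weeks, and 12% random dropout in controls. That is about 7 + 4 = 11 women, fewer than the 14 planned for. This mechanism is MAR.

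- Deleting in every trial: mean week-8 effect 0.15 SD when the truth is 0, and 0.90 SD when the truth is 0.75.
- Using all data under MAR: 0.00 and 0.75.

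The plan, however, would delete only where MCAR is accepted. With logistic slopes of 1 to 2 per SD and a pooled MCAR-type test at 5%, the departure was detected in about 25% to 58% of trials. Testing the mirror-therapy arm alone raised this to 71% to 86% (slopes 1.5 to 2). In the trials where the pooled test missed it, the mean completer effect was 0.07 to 0.16 SD under the null. Averaged over the whole two-step rule, at slopes of 1.5 to 2, it was 0.06 to 0.08 SD under the null and 0.84 to 0.85 SD when the truth was 0.75, an excess of 0.09 to 0.10 SD.

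**Step 3: imputation under MAR and MNAR.** Assume 35 per arm, AR(1) correlation 0.6, about 20% missing at 8 weeks, no true effect, 3,000 trials and standard imputation from earlier visits and group.

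| Missingness in one arm depends on | Bias (SD) | False-positive rate |
|---|---|---|
| the 4-week value, observed (MAR) | 0.01 | 5.3% |
| the unseen 8-week value (MNAR) | 0.16 | 9.5% |

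With 500 per arm the MNAR bias was 0.15 SD, so it is not a small-sample effect.

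**The case against.** Several points on the other side are sound.

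- **MCAR deletion is unbiased.** Under the condition the first rule states, the harm is lost precision and lost participants. A reader might infer that the rule itself biases the primary contrast by 0.15 SD. It does not: that figure applies where data that are not MCAR are deleted as if they were, and the plan sends data recognised as such to imputation.
- **Modified intention-to-treat is undefined here.** A modified set allows some exclusions, and the definition may stand in a document not shown. A reader might infer that the rule undoes intention-to-treat or contradicts the plan. The text shows tension with the principle, not contradiction.
- **The word for what is excluded is ambiguous.** It could mean the missing record, and entering observed values into the GEE fits that reading. The participant is the more natural meaning. If only the record is meant, Step 1 falls away, but the sentence still needs rewording and the MNAR point is untouched.
- **Imputation can carry an MNAR adjustment**, and the imputation model is commonly left to the analysis plan. But the article names non-random missingness and gives it the same remedy as MAR, with no adjustment mentioned. The MAR half of the sentence is appropriate, so it would be wrong to call the whole of it invalid.
- **Painful shoulders as the reason for leaving.** A reader might infer this because persistent shoulder pain is a listed adverse event and "The participant who reports adverse events will have the right to withdraw and get free treatment". The article also lets such women continue, and lists voluntary withdrawal without a cause. Informative dropout is possible; that it is the likeliest pattern, or concentrated in the mirror-therapy arm, is not documented.

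The trial also calls itself exploratory, which lowers the stakes but does not make the rule better.

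**Conclusion.** The concern holds in a limited form. On the natural reading, the exclusion rule discards valid observed data for no gain. Under true MCAR it causes no bias but raises the variance of the week-8 contrast by roughly 7% to 59%, depending on the missingness pattern, and removes randomised women. Choosing the method by a judgement of the mechanism is unreliable with about 14 expected dropouts among 70. If MCAR is wrongly accepted when dropout depends on earlier range of motion, the bias is about 0.15 SD where deletion is applied and about 0.06 to 0.10 SD over the two-step rule. Imputation as stated handles MAR but not MNAR; in the assumed example about 0.16 SD of bias remains.

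The dropout models, correlations, slopes and MCAR tests behind these sizes are assumptions, not figures from the article. The direction of the precision loss depends on none of them, nor does the fact that imputation under MAR does not correct MNAR.

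**What to change.** 1. Delete the sentence that excludes data judged missing completely at random.
2. Define the mITT set, and analyse every observed visit of all randomised women in it by one prespecified method valid under MAR, whatever any MCAR test shows. Either multiple imputation for everyone before the GEE, or a likelihood-based repeated-measures model, would serve. An unweighted GEE on available visits alone is assured only under MCAR.
3. Replace the non-random half of the imputation sentence with a delta-adjusted sensitivity analysis: shift the imputed values by a range of amounts and report where the conclusion changes.

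The cost is a change of wording and one extra analysis, with no change to visits, data collection or sample size. The article reports recruitment as ongoing, so the change could be made before the data are analysed.
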